### Sample size

2.12.

Power and sample size calculations were based on clinically meaningful differences between treatment groups with respect to changes in the outcomes across time (i.e. intervention effect). For the primary outcome - any SV/ARA perpetration at Time 3, the detectable difference between arms was calculated based on traditional methods that assumed a fixed number of clusters as well as fixed number of subjects per cluster [94]. Twenty-one clusters were randomized, assuming a within-cluster intra-class correlation (ICC) of 0.01 (within-school correlations for abuse perpetration, similar to our team’s prior work with a related sexual violence prevention program with male athletes [37,95]), and a 20% baseline SV perpetration rate in the control arm. With 866 participants (approximately 41 boys at each site) and an 80% retention rate at Time 3, we expect to have 80% power to detect an absolute difference in SV perpetration of 8.3 (42% relative decrease) due to the intervention. We anticipate having ample power to detect clinically meaningful changes in bystander behaviors and the secondary outcomes as well. Based on previous studies, the within-cluster ICCs for each of our secondary outcomes ranged from 0.006 to 0.01. If we assume the upper end of that range, we will have at least 80% power to detect standardized mean differences as small as 0.23 between study arms.

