#### Randomization

2.16.1.

Randomization was performed at the neighborhood level (i.e., cluster) to reduce risk for contamination. The initial randomization included 10 clusters that were assigned to experimental or control conditions. The study statistician performed this randomization, stratifying by lead site in that neighborhood (YMCA, Urban League, or Other), such that within each stratum, each site/neighborhood had a 50/50 chance of being assigned to intervention or control. Due to a combination of lower-than-expected recruitment by neighborhood (target = 96 participants each) and the interest from other community partners, we individually randomized an additional 11 neighborhoods, stratified by type of site. This resulted in a total of 21 clusters randomized, with 11 assigned to experimental and 10 assigned to control. All neighborhoods in the study met the original criteria of being socially or economically disadvantaged and/or predominantly African American.

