### Statistical methods

2.18.

Generalized linear mixed models will be used to account for the correlation among youth from the same cluster as well as the correlation between observations from the same youth. Descriptive statistics will be used to summarize the sample with regard to baseline characteristics of interest. Means and standard deviations will be presented for continuous variables, while sample proportions will be provided for categorical variables. 95% confidence intervals will accompany all sample statistics. Primary assessment of intervention effects will be based on intent-to-treat estimates. As-treated, or treatment-on-the-treated (TOT), effect parameters will be estimated in secondary analyses and reported as exploratory. Between-site differences regarding intervention effects will be assessed based on level of staff/facilitator engagement in curricular delivery as well as other observed external factors that may interact with the intervention to alter outcomes. SAS software will be used for all statistical analyses.

To assess differences at baseline between the youth in the experimental and control groups, demographics such as grade-level, race, nativity, and parental education will be compared while accounting for within-neighborhood clustering. Demographic variables as well as neighborhood-level characteristics resulting in between-arm imbalances will be considered as covariates in the primary and secondary analyses.

Participation bias will be assessed by comparison of age and race/ethnicity of youth participating in the study compared to the overall demographics of adolescents (school district and census data). Significant differences detected via chi-square analysis will be noted as potential validity threats.

An attrition analysis will be conducted by comparing youth who completed follow-up surveys with those who did not with regard to demographics as well as outcomes measured at baseline. All hypotheses will be two-sided tests with a significance level of 5%.

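### The 8.3-point and 0.23 SD detectable differences match an analysis of all 866 youth; at the stated 80% retention, power is about 74–75%, not 80%

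*Protocol article*

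**What the plan says.** Section 2.12 (Sample size) names a conventional method with fixed cluster numbers and fixed cluster sizes, "assuming a within-cluster intra-class correlation (ICC) of 0.01", and takes "a 20% baseline SV perpetration rate in the control arm". The sample is 866 youth, about 41 per site. The claim for the primary outcome is tied to retention: "an 80% retention rate at Time 3, we expect to have 80% power to detect an absolute difference in SV perpetration of 8.3" points, given as a 42% relative decrease. For the secondary outcomes, at the upper ICC of 0.01, it claims "at least 80% power to detect standardized mean differences as small as 0.23 between study arms".

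Section 2.16.1 (Randomization) gives the cluster split: "This resulted in a total of 21 clusters randomized, with 11 assigned to experimental and 10 assigned to control". Section 2.18 (Statistical methods) sets the test: "All hypotheses will be two-sided tests with a significance level of 5" per cent. Section 3 (Results) gives 464 youth in the experimental arm and 402 in the control arm.

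Section 2.12 states no baseline–follow-up correlation and no other reduction in variance.

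**The concern.** Every input needed to check the claim is printed, and the claim does not follow from them. Two figures on different scales, 8.3 points and 0.23 SD, both agree with a sample that has lost nobody, and both miss the sample left after the stated 20% loss. That pattern suggests an omitted step rather than rounding.

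The type II error at the stated effect would be about 25–26% instead of 20%. A non-significant primary result could then be read as excluding an 8.3-point reduction with more assurance than the design provides. The same applies to the secondary outcomes. Attrition is also the input least safe to omit here: section 4 (Discussion) calls retention a critical challenge and expects substantial missing data from rounds with justice-involved youth.

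**Working it through.** **Inputs.** 21 clusters, 866 enrolled, 80% retained at Time 3, ICC 0.01, control rate 20%, effect 8.3 points (so 11.7% in the intervention arm; 8.3/20 = 41.5%, printed as 42%), power 80% (all 2.12); two-sided 5% (2.18); arms 464/402 (3).

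**Formulas.** With N analysed, m = N/21 and DE = 1 + (m − 1) × 0.01. Effective size per arm is n = N/(2 × DE).
- Proportions (unpooled): d = (1.960 + 0.842) × √{[0.2 × 0.8 + (0.2 − d)(0.8 + d)]/n}
- Means: SMD = 2.802 × √(2/n)

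**1. The published figures, with no attrition.** N = 866, m = 41.2, DE = 1.402, n = 308.8.
- Detectable difference: 8.19 points (unpooled), 8.23 (pooled), 8.27 (unpooled, 464/402 split).
- Power at 8.3 points: SE = √[(0.160 + 0.1033)/308.8] = 0.0292; 0.083/0.0292 = 2.842; Φ(2.842 − 1.960) = 81.1%. Pooled 80.8%; with the 464/402 split, 80.3% (unpooled).
- SMD: 2.802 × √(2/308.8) = 0.2255, which rounds to 0.23. Power at 0.23 is 81.5%.

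Both published figures are recovered to within about 0.1 point and 0.005 SD.

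**2. The same calculation with the stated retention.** N = 866 × 0.8 = 692.8, m = 33.0, DE = 1.32, n = 262.4.
- Power at 8.3 points: SE = √(0.2633/262.4) = 0.0317; 0.083/0.0317 = 2.620; Φ(2.620 − 1.960) = 74.6%. Pooled 74.1%; 464/402 split (unpooled) 73.7–73.8%.
- Detectable difference at 80% power: 8.81 points (unpooled), 8.85 (pooled), 8.89 (464/402 split, unpooled). Relative decrease: 8.8/20 = 44% to 8.9/20 = 44.5%.
- SMD: 2.802 × √(2/262.4) = 0.245. Power at 0.23 is 75.0%.

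**3. Sample needed for the stated claim.** With 21 clusters, 80% power at 8.3 points needs about 832 (unpooled) to 842 (pooled) youth analysed. That is 832/866 = 96% to 842/866 = 97% retention.

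**4. Other routes to 80% with 693 analysed.**

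| Variant | Power at 8.3 points | Power at 0.23 SD | Fits the text? |
|---|---|---|---|
| ICC 0.006 | 78.4% | 79.2% | No: 0.01 is stated |
| One-sided 5%, t with 19 df | 80.6–81.1% | 81.4% | No: tests are two-sided |
| Baseline–follow-up correlation 0.34–0.36 | about 80% | about 80% | Not stated |
| Arcsine | about 74.7% | – | Still short |
| Continuity correction | 70.1% | – | Lower |

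**5. Sensitivity to the reference distribution.** With 21 clusters there are 19 between-cluster degrees of freedom. A t reference on 19 df at 80% retention gives about 70% power for both claims, with detectable differences of 9.2 points and 0.26 SD. The published figures match a normal reference: even with all 866 analysed, t on 19 df gives 8.6 points and 0.238 SD.

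**The case against.** The strongest reply is that section 2.12 opens by basing power on changes over time, and that the models in section 2.18 include the baseline outcome. A baseline–follow-up correlation of about 0.35, with 80% retention kept in, recovers both figures: at r = 0.35, 8.3 points (8.31 unpooled, 8.35 pooled) and 0.229 SD. The cited method is not at hand, so an omitted retention step is an inference. This much stands: the cause is not proved, and no attrition is the only explanation solely within the inputs the article states. The reply does not rescue the paragraph. For the primary outcome it describes a between-arm difference at Time 3 and lists its inputs, and no correlation is among them.

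Three smaller points have some force.
- With equal arms, the no-attrition figure rounds to 8.2. It reaches 8.3 only with the actual arm split and unpooled variance. It is still far closer to 8.3 than 8.8–8.9 is.
- The 0.23 SD sentence does not repeat the retention rate, and no Time 2 retention is given. Applying 80% there is a reading of the same paragraph. It is a reasonable one, since Table 2 compares secondary outcomes at Time 2 and Time 3.
- The article does not name a reference distribution, so the t(19) results are a sensitivity check and not part of the error.

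It can also be said that the gap is modest, that recruitment is over, and that a null result should be judged by its confidence interval. That bears on the consequences, not on whether the stated figure is right.

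**Conclusion.** The concern holds. On the article's stated inputs, power for an 8.3-point difference is about 74–75%, and the difference detectable with 80% power is 8.8–8.9 points. For the secondary outcomes, the figures at 80% retention are 75% power at 0.23 SD and 0.245 SD detectable. The shortfall is 5–6 points of power, or about 0.5–0.6 points of detectable difference: moderate in size, but the power claim for the primary outcome is wrong as written.

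This rests on ICC 0.01, 21 equal clusters, a 20% control rate, a two-sided 5% normal test and no gain from baseline adjustment. The first four are as stated, and the absence of any stated correlation is why the last is used. The SMD result also assumes that 80% retention applies to the secondary outcomes.

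**What to change.** Rewrite the power statement in section 2.12. With 80% retention (about 693 youth, 33 per cluster, ICC 0.01), the trial has 80% power for a difference of about 8.9 points (44–45% relative) and for 0.245 SD. Equivalently, it has about 74% power for 8.3 points. If a baseline–follow-up correlation or another assumption was used to reach 8.3 and 0.23, state its value and source instead.

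Name the reference distribution. If 19 between-cluster degrees of freedom are to be used, the figures become about 9.2 points and 0.26 SD, or about 70% power for 8.3 points. Since enrolment is complete, the trial team can base the restatement on the realised cluster sizes.

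The cost is one paragraph with slightly less favourable figures. Enrolment, design and analysis do not change.

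### The stated 80% power for 8.3 points and 0.23 SD is not reached by a two-sided 5% test on 21 clusters; at the plan's own 80% retention it is about 70%

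*Protocol article*

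**What the plan says.** The Sample size section gives the inputs: "Twenty-one clusters were randomized, assuming a within-cluster intra-class correlation (ICC) of 0.01", "a 20% baseline SV perpetration rate in the control arm", and "With 866 participants (approximately 41 boys at each site) and an 80% retention rate at Time 3". From these it concludes, for the primary outcome, "we expect to have 80% power to detect an absolute difference in SV perpetration of 8.3 (42% relative decrease) due to the intervention". For the secondary outcomes it reports that "the within-cluster ICCs for each of our secondary outcomes ranged from 0.006 to 0.01", takes the upper end, and concludes that "we will have at least 80% power to detect standardized mean differences as small as 0.23 between study arms". It describes the method only as a conventional one with the number and size of clusters held fixed. It names neither a normal nor a t reference and gives no degrees of freedom.

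The Randomization section gives the allocation: "This resulted in a total of 21 clusters randomized, with 11 assigned to experimental and 10 assigned to control". The Statistical methods section sets the test: "All hypotheses will be two-sided tests with a significance level of 5" per cent. The primary and secondary models include the baseline outcome, treatment group and a random effect for cluster. No small-sample degrees-of-freedom method is named.

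**The concern.** Treatment is assigned to clusters, so the arm effect is judged against variation between clusters. With 21 clusters in two arms, that variation is estimated on 21 − 2 = 19 degrees of freedom. The two-sided 5% critical value is then 2.093, not the normal 1.960. A power figure that ignores this is too high, and the error does not go away when attrition or cluster size is dealt with.

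What is at stake is the reading of the result. If the primary comparison is null, readers will use the printed power to judge how firmly an 8.3-point effect can be excluded. A trial with 70% power misses a true effect of that size three times in ten, against the two in ten that the plan advertises.

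**Working it through.** **Inputs.** From Sample size: 866 youth, 21 clusters, ICC 0.01, control rate 20%, difference 8.3 points (so 11.7% in the intervention arm), SMD 0.23, retention 80%. From Randomization: 11 versus 10 clusters. From Statistical methods: two-sided 5%. Clusters are taken as equal in size.

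**Formulas.**
- Design effect DE = 1 + (m − 1) × ICC; effective number per arm = n / DE.
- SE for the risk difference = √[0.117 × 0.883 / e1 + 0.20 × 0.80 / e2].
- SE for the SMD = √[1/e1 + 1/e2].
- Normal power = Φ(difference/SE − 1.960).
- t power = probability that a noncentral t on 19 df, with noncentrality difference/SE, exceeds 2.093.

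**Step 1. Look for the plan's own figures, all 866 youth.** m = 866/21 = 41.24, so DE = 1 + 40.24 × 0.01 = 1.402. Effective numbers at 11:10 are 323.5 and 294.1.
- SE (risk difference) = 0.02939; 0.083/0.02939 = 2.825; normal power 80.6%.
- SE (SMD) = 0.08057; 0.23/0.08057 = 2.855; normal power 81.4%.
- Differences detectable at 80%: 8.2 points and 0.226 SD.

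These match the printed 8.3 and 0.23, but only with the stated retention left out.

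**Step 2. Same inputs, t on 19 df.** Power is 76.4% for 8.3 points and 77.3% for 0.23 SD. With a 1:1 split it is 76.9% and 77.4%. For 80% power, about 8.6 points and 0.24 SD are needed.

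**Step 3. Apply the stated retention.** 0.80 × 866 = 692.8 youth; m = 33.0; DE = 1.320; effective numbers 274.9 and 249.9.
- SE (risk difference) = 0.03187; ratio 2.604.
- SE (SMD) = 0.08740; ratio 2.632.

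| Youth | Reference | Power, 8.3 points | Power, 0.23 SD | Detectable at 80% |
|---|---|---|---|---|
| 866 | normal | 80.6–81.1% | 81.4–81.5% | 8.2 points; 0.226 SD |
| 866 | t, 19 df | 76.4–76.9% | 77.3–77.4% | 8.6 points; 0.238 SD |
| 693 | normal | 74.0–74.6% | 74.9–75.0% | 8.8–8.9 points; 0.245 SD |
| 693 | t, 19 df | 69.5–70.1% | 70.4–70.5% | 9.2–9.3 points; 0.258 SD |

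Ranges cover an 11:10 and a 1:1 split.

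**Step 4. Separate the two causes.** At the stated retention, replacing the normal reference by t on 19 df lowers power from about 74–75% to about 70%, a loss of 4–5 points. Attrition alone, under the normal reference, takes it from about 81% to about 74–75%. Attrition is the larger cause, but correcting it does not remove the other.

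**Step 5. Other routes to the printed figures.** A one-sided 5% t test on 19 df with retention applied gives 80.6% and 81.4%, also a match, but it breaks the two-sided rule. A two-sided t on 19 df at ICC 0.01 gives neither figure, with or without attrition.

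**The case against.** **The cause is not identified.** A reader might infer that the authors used normal quantiles. The article does not say so, and the source cited for the method is not at hand. The normal match requires dropping the stated retention; the one-sided t match keeps retention but breaks the two-sided rule. This objection stands, and the point is limited accordingly: the printed figures are consistent with normal quantiles and no attrition, no more. Either route breaks one stated input, so neither rescues the figures.

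**The test level.** A reader might also infer that the trial will really test at about 6.5%, the two-sided tail of t on 19 df beyond 1.96. That would follow only if the final analysis used a normal reference. The article states 5% and leaves the degrees-of-freedom method open, which a statistical analysis plan would commonly settle. The documents do not support a claim about the actual type I error.

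**Baseline adjustment.** The planned models include the baseline outcome, which may recover precision. For the SMD, a baseline–outcome correlation of about 0.26 would restore 80% power at 866 youth, and about 0.45 at 693. Those correlations are assumptions. The Sample size section states none and claims no such gain, so it cannot support the printed figure. The possibility is still a reason not to say flatly that the trial itself is underpowered.

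**Rounding.** An unrounded 0.235 SD gives 79.0% at 866 youth, which nearly closes the secondary gap if nobody is lost, but only 72% at the stated retention. An unrounded 8.35 points gives 77.0% at 866.

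**Size.** The degrees-of-freedom effect is modest and recruitment is complete. That limits the weight of the point, not its correctness.

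**Conclusion.** The point holds in a limited form. The Sample size section prints a power that its own inputs do not give under a two-sided 5% test on 19 between-cluster degrees of freedom. The shortfall is 3–4 percentage points if all 866 youth are followed and about 10 points at the stated 80% retention, where power is about 70% for both 8.3 points and 0.23 SD. Of those 10 points, 4–5 come from the degrees of freedom and the rest from attrition.

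This rests on equal clusters, ICC 0.01, a 20% control rate and no gain from baseline adjustment. Fitting the three lead-site strata used in randomization would leave 17 degrees of freedom and lower power by about half a point. It is a correction that should be made, not a threat to the design. A figure of 77% would not be a sound restatement, because it still leaves out the retention that the plan itself assumes.

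**What to change.** Recalculate the Sample size paragraph with the t distribution on the between-cluster degrees of freedom (19) and the retained sample (about 693 youth, 33 per cluster), and name the reference distribution used. Restate the result as about 70% power for 8.3 points and for 0.23 SD, or as detectable differences of about 9.2–9.3 points and 0.26 SD at 80% power. If a gain from baseline adjustment is to be claimed, state the assumed correlation and show the figure with and without it.

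The cost is one rewritten paragraph with less favourable figures. No extra youth and no change of design are needed.

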### Recruitment

2.13.

For recruitment of eligible youth, we relied on the network of community partners we had identified in the asset maps created for each neighborhood cluster. This included site leaders, program facilitators, recruiters with strong connections to their community, prevention specialists embedded in schools, school districts that offer community-based programs as an alternative to suspension, and the Community Intensive Supervision Program (CISP) for youth involved in the juvenile justice system. Participant recruitment started in July 2015 and continued until the sample size met our estimates, through May 2017.

Using respondent driven sampling (RDS), former and current participants could refer their friends to the program. Participants interested in RDS received a packet of information on how to recruit a friend or neighbor and five recruitment coupons. When newly-recruited participants came to their first session and turned in their recruitment coupon, the peer recruiter was compensated $5, up to $25 overall.

### Assent and consent

2.14.

Adolescent males ages 13–19 received a description about the research study and parental letter about the study from the community sites. The parent letter included an option for parents/caregiver to decline their child’s participation. We received a waiver of parental permission and waiver of signed consent from the University of Pittsburgh Human Subjects Research Protection Office. Research assistants reviewed the verbal consent form with youth at the beginning of the first session and answered any questions pertaining to confidentiality, the program flow, and survey time points. The consent form covered all 3 waves of data collection, Time 1 through Time 3 as described earlier.

### Retention in program

2.15.

Once community partners recruit youth, retention throughout the 18-h curriculum is a key focus. Upon enrolling in either the control or experimental arm, prospective participants received program information, signed an assent form and completed a contact information sheet. Research assistants ensure that the document is legible and that all fields are completed. Research assistants use this information to contact the participant prior to each session to remind them of the session. If youth are not present at the beginning of a session, research assistants and facilitators will contact the participant to encourage them to join late.

### Assignment of interventions

2.16.

#### Randomization

2.16.1.

Randomization was performed at the neighborhood level (i.e., cluster) to reduce risk for contamination. The initial randomization included 10 clusters that were assigned to experimental or control conditions. The study statistician performed this randomization, stratifying by lead site in that neighborhood (YMCA, Urban League, or Other), such that within each stratum, each site/neighborhood had a 50/50 chance of being assigned to intervention or control. Due to a combination of lower-than-expected recruitment by neighborhood (target = 96 participants each) and the interest from other community partners, we individually randomized an additional 11 neighborhoods, stratified by type of site. This resulted in a total of 21 clusters randomized, with 11 assigned to experimental and 10 assigned to control. All neighborhoods in the study met the original criteria of being socially or economically disadvantaged and/or predominantly African American.

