Missing data were minimized as much as possible by keeping the surveys as short as possible to reduce survey burden, encouraging youth to be as complete and honest as possible by ensuring anonymity of the surveys, and working assiduously with community partners to ensure that youth stay engaged and can be tracked to complete follow up surveys. Mechanisms for missing data will be investigated by comparing important covariates between youth with and without missing data at each time point. We will characterize these mechanisms as 1) missing completely at random (MCAR), 2) missing at random (MAR), or 3) not missing at random (NMAR). If the nature of our missing data is ignorable (either MCAR or MAR), our primary analysis will be sufficient given that it is a likelihood-based approach to handling missing data. Additionally, we will conduct various sensitivity analyses such as multiple imputation via chained equations (MICE) and complete-case analyses. If our missing data is non-ignorable (MCAR), we will investigate other methods such as joint or shared parameter models.

The primary outcome for this study is reductions in self-reported perpetration of SV and ARA at Time 3, compared to controls. We will examine whether Manhood 2.0 results in improvements in the primary outcome assessed at 9 months after end of program (Time 3) compared to controls. Generalized linear mixed models (GzLMM) will be used and will include variables for baseline SV/ARA perpetration, treatment group, and random effects for cluster. For the primary outcome and other binary outcomes, the GzLMMs will be fit using a logit link; for all other continuous outcomes, an identity link function will be used.

For positive bystander intervention and the remaining secondary outcomes, the models will include variables for the secondary outcome at baseline, treatment group, and random effects for cluster. This will allow us to assess the effect of the study arm after accounting for clustering within neighborhoods. As an exploratory analysis, all three time points will be included in a single generalized linear mixed model to quantify the long-term trajectories of each of the secondary outcomes.

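### Allocation was stratified by type of site, but the stated primary and secondary models leave the stratum out, so the analysis does not follow the design; the effect on precision is probably modest and depends on how allocation was done.

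*Protocol article*

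**What the plan says.** Protocol article, section 2.16.1 (Randomization), describes two phases. The first 10 clusters were allocated by "stratifying by lead site in that neighborhood (YMCA, Urban League, or Other"), and within a stratum "each site/neighborhood had a 50/50 chance of being assigned to intervention or control". When recruitment per neighborhood fell short, "we individually randomized an additional 11 neighborhoods, stratified by type of site". The outcome was 11 experimental and 10 control clusters.

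Section 2.18 (Statistical methods) then names the model terms. The primary model "will include variables for baseline SV/ARA perpetration, treatment group, and random effects for cluster". For bystander behavior and the other secondary outcomes, "the models will include variables for the secondary outcome at baseline, treatment group, and random effects for cluster". Neither list contains the stratification factor. The moderator models in the same section also omit it.

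One clause in section 2.18 could let site type in: "Demographic variables as well as neighborhood-level characteristics resulting in between-arm imbalances will be considered as covariates in the primary and secondary analyses".

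**The concern.** A factor that restricted the randomisation belongs to the design, and the usual rule is to carry it into the model. Here the model terms are listed and the factor is absent. This is therefore a stated choice and not a detail left for the analysis plan.

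The imbalance clause is a poor substitute. It depends on the data and promises only consideration. It also works backwards for a stratification factor: the better the stratification balances site type, the less likely the clause is to admit it.

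Two things are at stake. If stratification did force balance, an unadjusted model keeps between-stratum variation in the error term and the test becomes somewhat conservative. If it did not, whether site type is adjusted for will be decided after the arms have been compared. With 21 clusters, chance imbalance is easy to get.

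**Working it through.** **Inputs.** From section 2.12 (Sample size): ICC 0.01, 866 participants, about 41 per cluster, 80% retention, control rate 20%, detectable difference 8.3 points (so 11.7% in the other arm). From section 2.16.1: 21 clusters. Retained youth per cluster: 866 × 0.80 / 21 = 33. The documents do not say how much of the between-cluster variance site type explains. Call that share R²; it is an assumption and is shown as a range.

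**The plan's own figure.** With 33 per cluster the design effect is 1 + 32 × 0.01 = 1.32, so the effective number per arm is 693 / 1.32 / 2 ≈ 262. The standard error is √[(0.20 × 0.80 + 0.117 × 0.883) / 262] ≈ 0.0317. Two-sided power is Φ(0.083 / 0.0317 − 1.96), about 74% to 75% depending on the variance formula, against the stated 80%. With all 866 analysed it is about 81%. That gap is a separate matter; here it shows only that precision is not plentiful.

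**Where the variance lies.** On a linear cluster-mean scale, with total variance 1:
- between clusters: 0.010
- within clusters: 0.99 / 33 = 0.030
- between share: 0.010 / 0.040 = 25%

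**Gain in standard error from adding the stratum.** The multiplier is √(1 − 0.25 × R²).

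| R² | multiplier | fall in SE |
|---|---|---|
| 0.10 | √0.975 = 0.987 | 1.3% |
| 0.25 | √0.9375 = 0.968 | 3.2% |
| 0.50 | √0.875 = 0.935 | 6.5% |
| 1.00 | √0.75 = 0.866 | 13.4% |

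**Cost in degrees of freedom.** Three levels use two extra parameters, so the between-cluster degrees of freedom go from 19 to 17 and the critical t from 2.093 to 2.110, or 0.8%. With perfect balance, this cost outweighs the gain when R² is below about 0.06.

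**Simulation.** Cluster-level data, 20,000 runs per setting, with assumed strata of 7, 5 and 9 clusters (the documents do not give the counts). CI change is the change in mean interval width from adding the stratum.

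| R² | Balanced within strata: type I error, unadjusted | CI change | Independent 50/50 draws: type I error, unadjusted | CI change |
|---|---|---|---|---|
| 0 | 5.0% | +1.4% | near 5% | +6.7% |
| 0.25 | 4.3% | −2.0% | near 5% | +3.2% |
| 0.50 | 3.7% | −5.6% | near 5% | −0.4% |
| 1.00 | 2.8% | −13.0% | near 5% | −8.1% |

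Under independent draws the cost at R² = 0 exceeds 0.8% because arm and stratum are then correlated by chance, and the adjusted contrast pays for that too.

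**The case against.** The strongest objection is that the mechanism is not established. Section 2.16.1 gives each site an even chance and says the later clusters were individually randomised; section 2.16.2 (Blinding) says this was done as each site was approved. No blocking is described. A reader might infer that the unadjusted standard error is simply too large and the test conservative. The documents do not support that flatly, because it needs balance to have been forced within strata. This part of the objection stands.

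The size is also open. Nothing in the documents supports any particular R². Baseline perpetration is already in the model and may absorb part of what site type would explain. The primary model uses a logit link, so the linear-scale arithmetic is approximate. All of this stands, which is why only ranges are given.

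It is also fair that the two phases may not share a factor: the first names three lead organisations, the second only type of site, and section 2.4.1 (Study setting) classifies sites differently again.

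The claim that the imbalance clause already deals with the point does not stand, since entry under it is conditional on the data. Nor does the appeal to an unseen analysis plan, because the article itself lists the model terms.

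**Conclusion.** The mismatch holds: both phases were stratified by a site factor, and neither stated model contains it. It does not inflate type I error, and nothing in the documents shows that it biases the estimate.

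Its effect on precision depends on two unknowns. If arms were balanced within strata, leaving the factor out makes the test mildly conservative, and adjusting saves about 1% to 6% of the standard error for R² of 0.1 to 0.5, with a ceiling of 13%, before the loss of two degrees of freedom. If the draws were independent, the gain is mainly protection against chance imbalance, and the interval narrows only when R² is about 0.5 or more.

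Two stronger readings should be avoided. One is that between-cluster variance is what limits precision here: at the planned ICC, 75% of the cluster-mean variance (0.030 of 0.040) is within clusters. The other is that a 12.5% fall in variance (R² = 0.5) is worth 1 / 0.875, or 14%, more youth. With 21 clusters fixed, only the within part shrinks as youth are added, and a total of 0.035 needs 0.99 / 0.025 = 39.6 per cluster against 33, or 20% more.

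**What to change.** Pre-specify the stratification factor actually used as a fixed effect in the primary and secondary models. Keep it whatever its p-value or observed imbalance, and use a small-sample degrees-of-freedom method. If it is to be left out, give the reason.

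State whether type of site in the second phase means the same three levels as in the first, with a rule for merging very sparse levels, and whether allocation was blocked within strata. Examine randomisation phase (first 10 against later 11 clusters) in a sensitivity model.

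The cost is one line of model specification, about two between-cluster degrees of freedom, and possibly a slightly wider interval if site type does not predict the outcome: in the simulation 1.4% under balanced strata and up to 6.7% under independent draws.
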